## Abstract

**Background:**

Youth facing barriers created by social marginalization are at a greater risk of adverse health outcomes, lower educational and occupational attainment, and decreased overall quality of life as adults. The negative psychosocial and physiological consequences of significant barriers to positive development during youth may be mitigated by interventions promoting physical activity, psychosocial development, and healthy behaviours. Sport for Development programming is a possible opportunity for youth facing barriers to engage in activities that foster positive youth development, which may improve socioeconomic outcomes, quality of life and long-term health status in this population. This paper outlines the study protocol measuring impact of an urban Sport for Development facility on positive youth development in youth facing barriers.

**Methods/design:**

Participants aged 6–29 will be recruited from programs at an urban Sport for Development facility to a 2-year prospective longitudinal mixed-methods study. Participants will be stratified by age into three cohorts with age-specific outcomes. Age-specific positive youth development outcomes will be assessed quantitatively by self-report and pedometer at baseline and after 6 months, 1-year, and 2-years of program participation. Focus groups will provide data regarding youth experience and the impact of facility and program components on youth outcomes.

**Discussion:**

Our findings will inform best-practice and feasibility of a Sport for Development facility delivering programs in a socially and economically challenged urban setting in a high-income country.

**Trial registration:**

ISRCTN67016999. Date of registration: October 22, 2019.

## Background

Significant barriers to positive development during youth including low socioeconomic status and other social marginalization can have negative consequences persisting into adulthood [1–4]. Physiological consequences of a stressful environment during youth confer increased risk of chronic stress related illnesses such as obesity, diabetes, cancer, and heart disease [5]. Similarly, adversity during childhood can impact the development of psychological and social functioning, further contributing to negative consequences during adulthood [6]. Persisting negative health and functional outcomes may impair attainment in other life domains such as academic, occupational, and civic engagement, limiting socioeconomic and quality of life potential and perpetuating a cycle of marginalization [7, 8]. The increased risk of poor health outcomes conferred by barriers faced during youth may be further compounded by self-regulatory problems which reduce the likelihood of engaging in healthy risk-mitigating behaviours and/or accessing appropriate care [9], while increasing the likelihood of engaging in risky behaviours [10–12].

A subpopulation of adults who faced significant barriers to positive development during youth develop no measurable negative consequences despite the adversity they have faced during childhood and are said to be “resilient” [5]. The quality of resilience is in part predetermined by genetics and psychobiological traits but may also be fostered through physical and psychosocial intervention [5]. Specifically, programs including physical activity, development of meaningful social connections, and deliberate cultivation of life skills are thought to be important factors for cultivating resilience in youth facing barriers [12–14], and may be protective against increased health and functional risk in this population.

Positive Youth Development (PYD) includes the promotion of personal characteristics described as life skills that enable individuals ‘to lead a healthy, satisfying and productive life’ and can be intentionally incorporated into sport programming [15, 16]. The development of personal assets through PYD sport programming supports an individual’s ability to engage in resilience-promoting behaviour. These positive skills and traits are transferable into adulthood and facilitate a person’s ability to engage in school and employment and participate meaningfully in social and cultural activities [8, 17], producing change that can be expected to contribute to health, social, and economic benefits on a broader social scale. In this way, PYD sport programming aimed at affecting health and function on an individual level also has implications for positive social change on a group or community level, which is more traditionally considered an objective of Sport for Development (SFD) programs. Typically, SFD and PYD remain distinct as fields of study, and the relationships between SFD and PYD through sport are not well defined, possibly due to general differences in populations and contexts of study (developed countries vs. underdeveloped countries; recreational activity vs. competitive sport setting). For an urban youth population at risk of adverse outcomes based on their developmental environment and experiences, programming designed to enhance personal assets and create social impact through intentional sport programming can achieve both PYD and SFD outcomes. This type of programming can be considered a public health intervention, as both PYD and SFD are expected to mitigate risk of adverse health and functional outcomes in youth facing barriers [9, 18, 19].

Meaningful outcomes achieved through intentional sport programming may be mediated by the PYD context, positive relationships, and explicit inclusion of life skills programming within physical activity-centred programming [18, 20–23]. Foundational to positive outcomes of sport programming is the physical and psychological safety of the PYD context [21, 24, 25], necessary for youth to engage fully. Further, relationships between youth and leaders in which leaders are relatable and act as role models, engaging youth to understand and address their individual needs to reach goals with a focus on the future is critical for uptake of programmatic intentions [20, 24, 26]. Leaders can also support development of peer-peer connections to foster a sense of belonging that contributes to both a sense of psychological safety and engagement and retention of youth participants [21]. Programs must have an explicit program theory with an intentional design that is appropriately suited to achieve the desired PYD or SFD outcomes, such as increased life skills and good health behaviours to support academic or occupational achievement [16, 24, 26–28]. Lastly, in sport-based programs, physical activity aimed at promoting the competence, confidence, knowledge, and motivation needed to engage in physical activity for life (termed ‘physical literacy’) [29] and explicit teaching of life skills using sport or physical activity participation as a learning context [20, 26, 27] are most suited for developing PYD assets that may be expected to lead to SFD outcomes.

SFD programs have demonstrated a range of benefits to youth facing barriers in a variety of studies conducted internationally, often assessing participation in a single short-term program; long-term longitudinal research is lacking. The programs studied also tend to lack use of a logic model or theory of change to explain the factors expected to lead to the attainment of the program’s objectives, whether PYD, SFD, or otherwise. Similarly, it may be expected that research on PYD through sport as evaluated by the transference of life skills through team or competitive sport participation may promote SFD and PYD outcomes in a different manner or to a different degree than community-based participatory programs. As such, the impact of a sustainable urban SFD facility promoting PYD through recreational sport plus (i.e. programs whose main objective is increased participation in sport and reducing barriers to entry to sport, but that also use sport to address broader social issues; secondary benefits can include development of life skills, education, and increased health) and plus sport (i.e. programs primarily designed to address social issues including health, education and employment that use sport as a tool to achieve some of their objectives) programming where youth may engage in several ongoing programs in addition to wrap-around services such as counselling, nutrition, and homework programs, is unknown. Further, a thorough understanding of the contextual factors of such a program and its participants is lacking, resulting in a paucity of evidence to inform best-practice for SFD and PYD through sport programs to optimize individual and community impact.

A large, long-term longitudinal study investigating PYD outcomes in a SFD facility for urban youth facing barriers that is based on a clear theory of change illustrating program components is therefore needed. This research is important for both theoretical and practical reasons, and addresses several future research directives published in the field including calls for mixed-methods, longitudinal, and evaluative studies that validate the development of life skills through sport and evaluate the impact of program type of PYD outcomes [26, 30–32]. The current study proposes that participation in theory-based SFD programming at a dedicated facility will lead to increased PYD outcomes in urban youth facing barriers to positive development with age-specific objectives outlined in Table 1 and further articulated in Fig. 1, the Maple Leaf Sports and Entertainment (MLSE) LaunchPad Theory of Change. Repeated measures ANOVAs will be used to explore the effect of long-term participation in MLSE LaunchPad programming on age-specific outcomes. Moderation analyses will be used to identify the impact of program dosage on the relationship between time and primary outcomes. Finally, regression analyses will be used to identify the predictors of primary outcomes to better inform programming.

**Table 1 Tab1:** Study Hypotheses

Primary Hypotheses	
We hypothesize that participation in MLSE LaunchPad programming and wrap around services will result in:	
a) For youth aged 6–12:	• Increased physical literacy • Increased physical activity [28] • Increased rates of continued participation in sport or physical activity [33]
b) For youth aged 12–18:	• Increased positive health behaviors relating to physical activity, sleep, nutrition, smoking, substance use and sexual activity [29, 34] • Increased life skills including critical thinking, resilience, self-esteem, self-regulation, social competence and grit [26] • Increase academic outcomes including school attendance, academic performance and high school graduation rates [26, 34] • Increased rates of continued participation in sport or physical activity [34]
c) For youth aged 19–29:	• Increased rates of placement in employment, apprenticeship, or continued training [26, 29] • Increased personal income • Increased rates of continued participation in sport or physical activity [34, 35]
Secondary Hypotheses	
We hypothesize that a) volume of participation and b) duration of participation will correlate positively with the primary outcomes listed above.

**Fig. 1 Fig1:**
[figure not shown]
The MLSE LaunchPad Theory of Change illustrates the expected outcomes of programs for the different age groups of participants in the short- and long-term, and potential pathways for participants to follow. Supportive resources available to participants at the facility in addition to programs are indicated; additional resources may be added throughout the study duration and will be described in future publications as required. The respective cohorts are represented by age group with expected geographical catchment area and resource allocation indicated. The type of programming expected to produce the intended outcomes for each cohort are listed. This Theory of Change is expected to present a possible evidence-based model for collaboration and innovation in the youth development sector

## Methods/design

### Study design

The MLSE LaunchPad trial employs a single-arm, non-randomized within subject quasi-experimental design following a cohort of 350 participants aged 6–29 years old over up to 2-years of self-selected participation in programming at MLSE LaunchPad, a Sport for Development facility in downtown Toronto, ON, Canada. Data collection methods utilize repeated measures of age-specific outcomes according to hypotheses outlined in Table 1 and further described in Table 3 using self-reports and pedometer data at baseline, 6 months, 12 months, and 24 months from baseline. Qualitative assessments will take place annually throughout the data collection period using focus groups with a subset of participants. This protocol was developed in the fall of 2016 and initiated in February 2017. These data will collectively be used to evaluate the effects of intentional sport programming in a community hub on PYD and SFD outcomes in urban youth facing barriers. Moderating variables including age, gender, race, household income, postal code, program type, volume of participation and duration of participation will be explored to understand possible explanatory individual and programmatic elements of significance.

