#### Sample size

Based on the number of variables planned for analyses in each cohort (see Table 1) [43], we will recruit *n* = 150 youth ages 6–12, *n* = 100 youth ages 13–18 years of age, and n = 150 youth ages 18–29. Statistical power calculations were conducted to justify the appropriateness of the proposed study sample sizes for each age group. For youth aged 6 to 12, statistical power for the primary outcome variable, physical literacy, was analyzed using pre-post MLSE LaunchPad member data on the PLAYself Physical Literacy Assessment tool. To achieve a large effect size (Cohen’s d > = .8; MLSE LaunchPad participant mean = 1201, SD = 258.8; study group mean = 1277), the power calculation performed suggests that the proposed sample size of 150 will yield 94.9% post-hoc power. Power calculations were conducted using data previously collected at MLSE LaunchPad for primary outcome variables of interest in the 13 to 18-year-old cohort (i.e., self-esteem, grit, resilience, physical activity status, and physical activity levels). To achieve large effect sizes for these variables, the proposed sample size of 100 will yield 99.5–100% post-hoc power. Lastly, for youth aged 19 to 29, to achieve a large effect size in the primary outcome variable, employment status, the proposed sample size of 150 will yield 100% post-hoc power (power calculated using data collected at MLSE LaunchPad).

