i. Physical activity minutes/day ii. Health Behaviours iii. Continued engagement in sport	One-week pedometry producing at least 3 days of valid data with a minimum wear time of 10 h/day Healthy Behaviour Questionnaire 6-item, author-designed scale used to measure behaviours relating to sleep, nutrition, physical activity, smoking, substance use, and risky sexual behaviour Self-report of regular sport/physical activity participation
Participants aged 18–29	
a) Employment	Indicator:
i. Employment Status ii. Personal Income	Self-report of placement in job, apprenticeship or training; full- or part-time Self-report of personal income level
b) Sport Participation	Indicator:
i. Continued engagement in sport	Self-report of regular sport/physical activity participation

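### The stated total of 350 does not match cohort targets that sum to 400, and the outcome tables use age bands that overlap at 12 and 18

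*Protocol article*

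**What the plan says.** **Total.** The Study design section (Protocol article) describes a single-arm study "following a cohort of 350 participants aged 6–29 years old". The Sample size section sets a target for each cohort: "150 youth ages 6–12", then "100 youth ages 13–18 years of age, and n = 150 youth ages 18–29". The power statements in that section use n = 150, 100 and 150 for the youngest, middle and oldest cohorts.

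**Age bands.** The abstract says "Participants will be stratified by age into three cohorts with age-specific outcomes", so a participant's band decides which outcomes apply. The Study design section points to Tables 1 and 3 for those outcomes. Table 1 (Background) heads its middle group "b) For youth aged 12–18", next to a youngest group of 6–12. Table 3 (Outcomes) repeats 12–18 and heads its oldest group "Participants aged 18–29". Table 2, the Core programming text, the Data analysis section and the Discussion use 6–12, 13–18 and 19–29.

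**The concern.** A protocol should have one planned sample size. Here a reader cannot tell whether recruitment is complete at 350 or at 400. If it is 350, the reader cannot tell which cohort gives up the missing 50.

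The bands matter because the cohorts do not share outcomes. The youngest is assessed on physical literacy, physical activity and sport participation. The middle one is assessed on life skills, academic results and health behaviours, including smoking, substance use and sexual behaviour. The oldest is assessed on employment, income and sport participation. Under Tables 1 and 3 a 12-year-old belongs to both of the first two groups. Under Table 3 an 18-year-old belongs to both of the last two. The Ethics section asks for parental consent with assent below age 13, which is one more reason for the instruments given to 12-year-olds to be stated without ambiguity.

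**Working it through.** **1. The total.** Inputs are the three targets in the Sample size section.

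150 + 100 + 150 = 400, against 350 in Study design. The difference is 50, which is 50/400 = 12.5% of the summed targets. Treating 350 as the number left after attrition would need a 12.5% loss, and the article states no such rate.

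**2. Do the power figures go with 350 or 400?** Inputs for ages 6–12, from the Sample size section: means 1201 and 1277, SD 258.8, n = 150, stated power 94.9%. No significance level is stated, so two-sided 5% is assumed.

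- Standardised difference: d = (1277 − 1201)/258.8 = 76/258.8 = 0.2937.
- One-sample normal approximation: power = Φ(d√n − 1.96).
- At n = 150: Φ(0.2937 × 12.247 − 1.96) = Φ(1.637) = 94.9%, which reproduces the stated figure.

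The other two power statements use n = 100 and n = 150, the same as their recruitment targets. All three therefore go with the 400 split. The means, SDs or rates behind the two older cohorts' figures are not given, so those figures cannot be re-derived.

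**3. If 350 were the true total.** A proportional cut gives 350 × 150/400 = 131.25 and 350 × 100/400 = 87.5, or 131/88/131 after rounding.

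| Where the 50 are lost | n, ages 6–12 | d√n − 1.96 | Power, ages 6–12 |
|---|---|---|---|
| Only from the older cohorts | 150 | 1.637 | 94.9% |
| In proportion | 131 | 1.401 | 91.9% |
| All from ages 6–12 | 100 | 0.977 | 83.6% |

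For the older cohorts, take d = 0.8 as an assumed large effect. Even n = 50 gives Φ(0.8 × 7.071 − 1.96) = Φ(3.697), above 99.9%.

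**4. Age bands side by side.**

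| Place in the article | Youngest | Middle | Oldest | Overlap |
|---|---|---|---|---|
| Table 1 | 6–12 | 12–18 | 19–29 | 12 |
| Table 3 | 6–12 | 12–18 | 18–29 | 12 and 18 |
| Sample size, recruitment targets | 6–12 | 13–18 | 18–29 | 18 |
| Sample size, power text | 6–12 | 13–18 | 19–29 | none |
| Table 2, Core programming, Data analysis, Discussion | 6–12 | 13–18 | 19–29 | none |

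The Sample size paragraph labels the oldest cohort in two ways: 18–29 for recruitment and 19–29 for power.

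**The case against.** The best defence is that the dedicated Sample size section gives three explicit targets with power attached, while 350 appears once, in a one-line design summary. If 350 is simply a slip, no cohort falls short and no power figure changes. That stands, and it is why the power loss can be stated only conditionally. One could also read 400 as the number recruited and 350 as the number followed, but nothing in the text says so.

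A reader might infer that the power calculations themselves contradict each other. They do not: each uses its own cohort's recruitment target, and the one that can be checked reproduces. The different labels for the oldest cohort in that paragraph are a mismatch of wording, not a second power figure.

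A reader might also infer that participants aged 12 or 18 could be analysed in whichever of two cohorts is convenient. The Data analysis section does not leave that open, because its bands do not overlap, and Table 2 assigns evaluation tools by the same bands. Nor is the overlap at 18 present everywhere: Table 1 has none.

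Finally, the article gives no age distribution, so the number of participants aged 12 or 18 cannot be derived from it. What survives is that the tables named as defining the outcomes, and one recruitment target, disagree with the scheme used elsewhere.

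**Conclusion.** Wrong as written, on two separate counts.

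- **Total.** 350 and 400 cannot both be the planned sample size, and the article gives nothing that reconciles them. The gap is 50 participants. The power figures support the 400 split. If 350 is nevertheless correct, power for ages 6–12 lies between 83.6% and 94.9%, depending on where the 50 are lost, with about 92% under a proportional cut. This assumes a two-sided 5% one-sample test and the article's own means and SD. At an assumed d = 0.8, the older cohorts would barely be affected. A flat statement that some cohort is underpowered would go beyond the document.
- **Age bands.** Outcome assignment is ambiguous at age 12 in Tables 1 and 3 and at age 18 in Table 3. Age 18 also falls under two recruitment targets. The non-overlapping scheme used for analysis is already in the article, so this is an inconsistency to correct and does not show that any analysis is undefined.

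**What to change.** 1. State one total with its split, in both Study design and Sample size. Either use 400 = 150/100/150, which leaves the power figures as they are, or use 350 with three revised targets and power recomputed for each. If 350 is meant as the number retained from 400, say so and give the attrition allowance.
2. Change the band headings in Tables 1 and 3, and the oldest-cohort recruitment target in Sample size, to the 6–12, 13–18 and 19–29 bands used for analysis.
3. Add one sentence assigning each participant's cohort by age at baseline, so that these bands apply at a defined time point.

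The cost is wording, plus one recalculation if 350 is kept, in which case the stated power for ages 6–12 may be somewhat lower. The design and the analyses do not change.

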### Ethics

All procedures have been approved by the Community Research Ethics Office and amendments will be reviewed and approved by this same ethics review body for scientific content and compliance with applicable research and human subject regulations. Informed consent will be obtained from participants aged 13 years and older and participant assent and parental consent will be obtained from participants under the age of 13 years prior to data collection. Consent/assent procedures will be conducted by a trained staff member conveying full assurance to prospective participants that their participation will not impact programming availability or access and is entirely voluntary. Additional consent will be obtained for all qualitative data collection processes. Informed consent processes will follow the Community Research Ethics Office guidelines, which adhere to the 2014 Tri-council Policy Statement on Ethical Conduct for Research Involving Humans and will be completed in accordance with the MLSE LaunchPad Privacy and Data Collection Policies [25].

### Study population

#### Inclusion criteria

Participants will be eligible for the study given the following criteria upon enrolment for the study:
Age 6–29 yearsRegistered member of MLSE LaunchPadAttending programming at MLSE LaunchPadAbility to speak, understand and read EnglishPhysically able to participate in programming with or without the use of assistive devices-Recruited within 8 weeks of commencing program participation.

MLSE LaunchPad defines ‘youth facing barriers’ as ‘youth who may need greater supports and services to reach their full potential’, including low income, racialized, Indigenous, new to Canada, LGBTQ2S, and homeless or underhoused youth; youth in care or leaving care; and youth in conflict with the law. Demographic data will be collected in self-report surveys and through member registration and used to define characteristics of the population. No formal process is used to ensure youth accessing MLSE LaunchPad’s programs meet the stated criteria for ‘youth facing barriers’, and no youth are excluded from programming based on these criteria; however, the neighborhood demographics and outreach strategy have to date resulted in program participation by youth who meet the criteria outlined.

